5.3.6.4 Follow-up of Discontinuations

Subjects who receive at least one study vaccine and are discontinued will be followed for safety until the end of study, Day 228, if so allowed by the subject.

5.3.7 Medical History

The medical history should record significant problems active at the time of screening and within the prior year. Problems that have been clinically inactive within the prior year, but which might alter the subject’s current or future medical management, should also be noted (e.g. known mitral valve prolapsed or history of seizure disorder). Completely resolved past problems with no impact on current medical management (e.g. a healed fracture) may be omitted.

5.4 Modification of the Trial and Protocol

Modifications to the protocol should be made as an amendment and should be approved/acknowledged both by Medicago R&D Inc. and the IEC/IRB prior to being implemented unless the amendment is made to eliminate an immediate hazard to the clinical study subjects. Medicago R&D Inc. shall be responsible for notifying the regulatory authority, BGTD, Health Canada, of any substantial amendments to the protocol.

The Investigator is responsible for notifying the IEC/IRB of all protocol amendments.

Administrative amendments (e.g. changes in telephone number, etc.) will not require approval by the IEC/IRB unless requested by them.

5.5 Interruption of the Trial

The study may be interrupted or terminated by the Investigator following consultation with the Sponsor, by the Sponsor, or by regulatory authorities. The Investigator will immediately, on discontinuance of the clinical trial at the clinical site, inform both the clinical trial subjects and the IRB/IEC responsible for the study of the discontinuance, provide them with reasons for the discontinuance and advise them in writing of any potential risks to the health of the clinical trial subjects or other persons. It is the Sponsor’s responsibility to report discontinuance of the study to the regulatory agencies, within the appropriate timeframe and providing them with the reasons for the discontinuance, and advise them in writing of any potential risks to the health of clinical trial subjects or other persons. The Sponsor must then inform the Investigator that the appropriate notifications were made.

6.0 TREATMENTS

6.1 Vaccines Administered

This is a study of two (2) i.m. doses of plant-based H5 VLP (H5N1) pandemic influenza vaccine, at three dose levels (5µg, 10µg or 20µg), administered 21 days apart. Each vial of study vaccine will be combined with Alhydrogel® 1% (aluminium hydroxide, composed of Alhydrogel® 2% from Brennentag diluted in a ratio 1:1 with sterile water).

6.2 Identity of Investigational Product

The investigational product is a H5N1 (virus strain A/Indonesia/5/05, clade 2.1) pandemic influenza vaccine consisting of hemagglutinin (H5) protein VLPs produced in a plant-based *(N. benthamiana)* transient expression system. The transfer vector used to insert the plasmids (containing the constructs for proteins of interest) into the plant for expression is a bacterium, *Agrobacterium tumefaciens.*

Transient expression is a protein expression technology which does not require or use the stable integration process of a foreign gene into the host genome. Transient expression can be achieved by various means, but generally implies the use of a “transfer vector,” bacterial, viral or purely mechanical, which mediates the passage of genetic information in the form of a polynucleotide (in this example, a strand of DNA) into a host cell. Once in the cell, the genetic information is generally used directly as a template for transcription into mRNA molecules which are subsequently translated into a protein by the host cellular machinery. For further information refer to the Investigator Brochure.

6.2.1 Composition

The H5 VLP vaccine is a clear liquid suspension consisting of Hemagglutinin (H5) protein VLP’s (virus strain A/Indonesia/5/05, clade 2.1) of an approximate molecular weight of 72 kDa, in a PBS buffer (100mM PO_4_, 150mM NaCl, 0.01%Tween 80; pH 7-7.6). The H5 protein concentration in the vaccine will be 50µg/ml, 25µg/ml or 12.50µg/ml for final dosages of 20µg, 10µg or 5µg, respectively.

6.2.2 Preparation and Administration

Subjects will receive two 0.5ml intra-muscular doses of H5 VLP (H5N1) pandemic influenza vaccine combined with Alhydrogel® 1%, in the deltoid muscle, preferably in the non-dominant arm, twenty-one (21) days apart. Whenever possible, the injection will be given in the opposite arm from which serum samples are drawn. The H5 VLP influenza vaccine will be contained in a 2ml borosilicate vial (type 1) consisting of a volume of 0.6 ml of vaccine at concentrations of 50µg/mL, 25µg/mL or 12.5µg/mL, for the doses of 20µg, 10µg and 5µg, respectively. For the final dose administered, each of these will be diluted with 0.15mL of 1% Alhydrogel® (provided separately, 1.0mL per vial) to yield a total of 0.75mL of formulated vaccine in each vial. Each subject will be administered 0.5mL, resulting in final dosages of 20µg, 10µg or 5µg, respectively. Rubber stoppers should never be removed from any vial. The remaining 0.25 ml of vaccine in each vial will be discarded. The 0.5mL vaccine dose administered as well as the discarded 0.25mL will be recorded on the study vaccine accountability log.

Study vaccine or placebo will be administered by an un-blinded staff member who will not participate in any other aspects of the study.

The following steps should be taken to prepare study vaccine mixed with 1% Alhydrogel®:

- 1. Clean the surface of the H5 VLP vaccine vial (0.6mL) stopper with an isopropyl alcohol swab and allow the antiseptic to dry completely.
  2. Vigorously shake the Alhydrogel® 1% vial by inverting 5 – 6 times to ensure the suspension is mixed appropriately (uniform distribution of the white gel).
  3. Clean the surface of the vial stopper of the Alhydrogel® 1% with an isopropyl alcohol swab and allow the antiseptic to dry completely.
  4. Draw a volume of air equal to the amount of Alhydrogel® 1% (0.15mL) to be withdrawn from the vial into a disposable 1 mL plastic syringe.
  5. Pierce the vial stopper of Alhydrogel® 1% vial with the sterile needle attached to the syringe.
  6. Turn the vial upside down and inject the air from the syringe.
  7. Immerse the needle into the Alhydrogel® 1% suspension, keeping the needle immersed; withdraw the desired volume of 0.15mL.
  8. Inject immediately the content of the syringe into the study vaccine vial that has been wiped with an isopropyl alcohol swab at step 1 (total volume now 0.6mL + 0.15mL = 0.75mL.
  9. Invert and shake the study vaccine vial 5 to 6 times to ensure the investigational product and Alhydrogel® 1% are combined appropriately.
  10. Each subject will be administered 0.5mL, resulting in final dosages of 20µg, 10µg or 5µg, respectively
  11. The remaining 0.25 ml of vaccine in each vial will be discarded and recorded in the study vaccine accountability log.
  12. Discard the remaining 0.85mL of Alhydrogel® 1% and record in the study vaccine accountability log.
  13. DO NOT VORTEX the vaccine preparations.
  14. **Reconstituted study vaccine and Alhydrogel® 1% MUST be administered to the subject within 5 to 45 minutes.**

The needle on the H5 VLP influenza vaccine combined with Alhydrogel® 1% syringe should be changed prior to administration to the subject. A separate sterile syringe and needle should be used for each injection to prevent transmission of any infectious agents.

**Plant-based H5 VLP (H5N1) pandemic influenza vaccine must not be administered intravenously.**

Prior to vaccine administration to the study subject, clean the skin over the deltoid muscle with a suitable antiseptic (e.g., isopropyl alcohol) and wipe dry with a clean, dry gauze. The needle used for the injection should be of sufficient length to reach the substance of the muscle (at least one inch or 2.5 cm or longer based on the subject’s weight). Following needle insertion into the deltoid muscle, the end of the syringe should be stabilized and the piston of the syringe pulled back to ensure the needle has not entered a blood vessel. If blood is aspirated, the needle should be withdrawn, and a new injection prepared and administered. Documentation of the blood-aspirated dose should be noted on the site vaccine accountability log for monitoring purposes.

The placebo preparation will be a phosphate buffer (100 mM phosphate buffer + 150 mM NaCl + 0.01% Tween 80) combined with Alhydrogel® 1%. The phosphate buffer (labelled placebo) will be contained in a 2 ml borosilicate vial (type 1) consisting of a volume of 0.6 ml of placebo per vial. For placebo administration, 0.6ml vials will be diluted with 0.15ml of 1% Alhydrogel® (provided separately, 1 ml per vial) to yield a total of 0.75ml of formulated placebo in each vial. Each subject will be administered 0.5ml of the placebo. The remaining 0.25 ml of placebo in each vial will be discarded. Administration of the placebo preparation and discarding of remaining placebo will be recorded in the study vaccine accountability log.

Alhydrogel 1% should be stored at room temperature in a secured location. Further specific information relating to storage and shipment of study vaccines and the placebo preparation will be presented in the Study Procedures Manual.

6.2.3 Precautions for Use

Plant-based H5 VLP (H5N1) pandemic influenza vaccine must not be administered intravenously. The test articles should be stored at 2ºC to 8ºC. Do not freeze vaccine as this destroys activity. **Do not use vaccine that has been frozen.**

6.2.4 Dose Selection and Timing

Thirty-six (36) subjects will be randomized to receive two (2) i.m. injections, 21 days apart, of either 5µg or 10µg or 20µg H5 VLP (H5N1) pandemic influenza vaccine combined with Alhydrogel® 1%.

H5 VLP influenza vaccine lot number:

Dose of 5 µg Lot number: PS-130709-111 Expiry date: October 23^rd^ 2009

Dose of 10 µg Lot number: To be confirmed Expiry date: To be confirmed

Dose of 20 µg Lot number: To be confirmed Expiry date: To be confirmed

6.3 Identity of the Control Product

The control product (placebo) will consist of a 100mM phosphate buffer + 150mM NaCl + 0.01% Tween 80 and which will be combined with Alhydrogel® 1% in vials.

Lot Number: E101 and WFI 1:1 Lot Number : E201

Expiry date: December, 2010

6.3.1 Composition

The control product (placebo) will consist of a volume of 0.6mL -100mM phosphate buffer + 150 mM NaCl + 0.01% Tween 80 and will be combined with 0.15mL Alhydrogel® 1%.

6.3.2 Preparation and Administration

Subjects will receive two intra-muscular doses of 0.5mL, 100mM phosphate buffer + 150mM NaCl + 0.01% Tween 80 combined with Alhydrogel 1% (final concentration of 0.4%).

As the volumes and color of the study vaccine and the placebo control and adjuvant, as described above, are the same, the randomization of each subject to treatment or placebo will be maintained. However, the dose-concentration will not be blinded to the clinic staff.

6.3.3 Precautions for use

There are no known precautions for use.

6.4 Identity of Other Products

There will be no other products tested in this clinical trial.

6.5 Product Logistics

6.5.1 Labelling and Packaging

It is the responsibility of the Sponsor to ensure that supplies provided for this study are manufactured under Good Manufacturing Practices (GMP) and are suitable for human use. It is the responsibility of the Sponsor to ship a sufficient amount of dosage units to allow the clinical site to maintain an appropriate supply for the study.

The study vaccine and placebo will be labelled in accordance with all applicable regulatory requirements. All products will be placed in secondary packaging and appropriately labelled.

6.5.2 Storage and Shipment Conditions

Included in the shipment to the clinical site will be the test article, study vaccine H5 VLP (H5N1) pandemic influenza vaccine vials and Alhydrogel® 1%, the control product. A shipment requisition, preparation and expedition form will be included in the shipment, as well as an electronic temperature monitor device known as a “Temptale” and an electronic temperature monitoring device form will also be included. It is requested that the “Temptale” device be stopped upon receipt of the vaccine and the exact date and time is recorded on the “Temptale” form. A pre-addressed envelope for the “Temptale” return to Medicago will be included in the shipment. The vaccines will be immediately placed in the site refrigerator which has been stabilized at a temperature of 2ºC to 8 ºC.

Written authorization will be required from the Project Leader, [name], prior to administering the study vaccine.

The study vaccines will be stored in a secured, monitored refrigerator and maintained between 2ºC and 8 ºC. A manual log and calibrated thermometer or other temperature recording device will be used to document refrigerator temperature from the time of vaccine receipt and twice (2X) per day during the dosing period. This documentation will be maintained and made available to the Sponsor or designee for review. The site should ensure that appropriate back-up procedures are established for maintenance of the refrigerator temperatures, in the event of a power failure. Such procedures may include an alarm system, back-up electrical system/generator, or a documented contingency plan for maintaining proper refrigeration.

In the event the refrigerator deviates from the 2ºC to 8 ºC required temperature range, the site will do the following:

- As soon as an excursion is discovered, immediately quarantine product involved and contact the Project Leader, [name] at [contact] Ext. 137 or [contact].
- **DO NOT USE PRODUCT** if temperature excursion is outside of the 2ºC to 8 ºC range. Additional vaccine may need to be provided and the site will be advised regarding the immediate return of the compromised product (instruction to be provided by the Sponsor or their designee);
- Report the deviation to the Project Leader, [name], as well as the Clinical Monitor by preparing a memo that will include the following information:
  - A complete list of the product involved including the protocol number, Investigator name, product name, lot numbers, number of vials, date, the name of the person to contact for additional information, and the signature of the person completing the memo and date.
  - An explanation of the temperature deviation including the date and time the product was received and placed in the refrigerator, the date and time the temperature was last within the normal range, the total amount of time the refrigerator was out of range (hours and minutes) and the out of range temperatures reached.
  - Attach temperature logs for the out of range period to the memo.
  - Forward the memo, along with copies of the appropriate temperature logs, to the Project Leader and Clinical Monitor.

The site should maintain an S.O.P. relating to cold-chain maintenance. The Investigator has overall responsibility for ensuring that study vaccines are stored in a safe, limited access location under the specified appropriate storage conditions. Responsibility may be delegated to a nominated member of the study staff, but this delegation must be documented.

6.5.3 Product Accountability

The study vaccines (test articles) must be used only as directed in the protocol. Vaccines used during the course of the study will be recorded on the Study Vaccine Accountability Log. Any unused vaccine will also be accounted for on the Study Vaccine Accountability Log. The Investigator will be provided with the appropriate forms to ensure accurate, written records are maintained for receipt and disposition of all vaccines received from Medicago Inc.

6.5.4 Replacement Doses

Study vaccine replacement doses will be shipped according to dose level and may be used in the event of breakage or accidental loss while being prepared. All instances must be documented on the Study Vaccine Accountability Log.

6.5.5 Return of Unused Products

The Investigator or designee will sign all study vaccine accountability forms at the end of the vaccination period. Used and unused test article vials must be retained until the study monitor completes reconciliation of test article delivery records with disposition records and accountability of used and unused vials. All test articles must be accounted for and all discrepancies documented accurately. After drug accountability monitoring is completed, the Investigator or designee will return used and unused vials in accordance with instruction provided to:

**Attn: [name]**

6.6 Randomization/Allocation Procedures

The site will be provided a pre-determined sequence of randomization numbers according to the randomization code. Potential study subjects will be screened in a sequential fashion. Once screening is completed and study eligibility is confirmed, the randomization numbers of the pre-determined sequence will be allocated sequentially to subjects within the appropriate treatment group. Once a randomization number has been assigned, it will not be re-used in any event. No subjects will be entered into the study more than once. If a randomization number has been allocated incorrectly, no attempt will be made to remedy the error once study vaccine has been dispensed. The subject will continue with the randomization number and study vaccine. The study staff will notify the Sponsor as soon as the error is discovered without disclosing the study vaccine administered. Admission of subsequent eligible subjects will continue using the next unallocated number in the sequence.

Once it is determined that a study subject is eligible for randomization, a three-digit randomization number, (e.g. 101, 102, 103) and treatment will be assigned. This randomization number and treatment will be recorded along with the two-digit screening number for each subject on the Study Vaccine Accountability Log.

6.7 Blinding and Code Breaking Procedures

The randomization code will not be broken except in emergency cases wherein the identification of the treatment is necessary for appropriate treatment of the subject. A sealed envelope containing the un-blinded randomization schedule may be kept in a locked, secured location at the clinical site. In such circumstances, the un-blinded randomization code may be opened with the permission of the Sponsor Medical Monitor and the treatment assignment would be revealed.

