The safety experts will be provided the following blinded solicited local and systemic symptoms tabulated for the first 7 days post-vaccination: erythema (redness), swelling and pain at the injection site. The following blinded systemic symptoms will be provided for review: occurrence of headache, fever, myalgia (muscle aches), arthralgia (joint aches), fatigue, chills, and feelings of general discomfort or uneasiness, swelling in the axilla, groin, neck or chest, as well as the occurrence of any adverse or serious adverse events. Oral temperature results from the first seven days post vaccination will also be provided. These data may be un-blinded based on the reviewer’s medical judgement. Refer to Section 9.1.8 for further information.

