5.1.2 Trial Design and Plan

Subjects will be enrolled in the study in a staggered fashion. Refer to Figure 2 below. Study enrolment will begin with two (2) subjects from Cohort 1 on Day 0; one subject will be randomized to receive the 5µg dose of plant-based H5 VLP (H5N1) pandemic influenza vaccine combined with Alhydrogel® intramuscularly and one subject will be randomized to receive the placebo preparation, 100mM phosphate buffer + 150mM NaCl + 0.01% Tween 80 combined with Alhydrogel®. Subsequently, the following day, 3 subjects will be randomized to receive H5 VLP (H5N1) pandemic influenza vaccine and 1 subject will be randomized to receive the placebo preparation. On Day 2 of the study, 4 subjects will be randomized to receive H5 VLP (H5N1) pandemic influenza vaccine and 1 subject will be randomized to receive the placebo preparation. On Day 3 of the study, 4 subjects will be randomized to receive H5 VLP (H5N1) pandemic influenza vaccine and 1 subject will be randomized to receive the placebo preparation, for a total Cohort of 16 subjects. Once all Cohort 1 subjects have completed Day 7, a blinded safety report will be generated and reviewed by a panel consisting of the Investigator and two independent, expert medical advisors. A favourable 7-day safety report will permit the initiation of the vaccination of Cohort 2 at the 10µg dose level. A second blinded safety report will be conducted following the second vaccination at the 5µg dose level. A blinded seven-day safety report evaluating the safety of subjects receiving the 10µg dose will be generated in the same manner, in addition to a safety report being generated seven days following the second 10µg dose of study vaccine. Study vaccine dose escalation to 20µg will only be permitted if safety data is favourable, as judged by the Investigator and medical safety experts. Safety reports will be generated following the first and second dose of vaccine at the 5 µg and 10µg dose levels, and after the first dose of the 20µg dose level is completed, for a total of 5 reports.

The proposed randomization schedule is described below.

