9.1.6 Causal Relationship

The Investigator must make the determination of relationship to the test article for each adverse event. The Investigator should decide whether, in his/her medical judgement, there is a reasonable possibility that the event may have been caused by the investigational vaccine. If there is any valid reason, even if undetermined or untested, for suspecting a possible cause-and-effect relationship between the investigational vaccine and the occurrence of the adverse event, then the adverse event should be considered “definitely related,” “probably related” or “possibly related”. Otherwise, if no valid reason exists for suggesting a possible relationship, then the adverse event should be classified as “probably not related.” The following guidance may be helpful:

**Probably Not Related**: There is no medical evidence to suggest that the AE is related to the test article. The event can be readily explained by the subject’s underlying medical condition or concomitant therapy or lacks a plausible temporal relationship to the test article.

**Possibly Related**: A direct cause and effect relationship between the test article and the AE has not been demonstrated but there is a reasonable possibility that the event was caused by the test article.

**Probably Related**: There probably is a direct cause and effect relationship between the AE and the test article. A plausible biologic mechanism and temporal relationship exist and there is no, more likely explanation.

**Definitely Related**: There is a direct cause and effect relationship between the AE and the test article.

The medical assessment of intensity will be determined by using the following definitions:

**Mild:** The adverse event is easily tolerated and does not interfere with usual activity.

**Moderate:** The adverse event interferes with daily activity, but the subject is still able to function.

**Severe:** The adverse event is incapacitating and the subject is unable to work or complete usual activity.

The outcome may be classified as resolved, ongoing, resolved with sequelae, or death.

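### The emergency-only code-break rule conflicts with un-blinding at the 7-day reviews, and the accountability log and single envelope add routes by which the Investigator can learn codes while still judging causality

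*Protocol*

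**What the plan says.** **The rule.** Section 6.7: "The randomization code will not be broken except in emergency cases wherein the identification of the treatment is necessary for appropriate treatment of the subject". In that case "the un-blinded randomization code may be opened with the permission of the Sponsor Medical Monitor". The same section adds: "A sealed envelope containing the un-blinded randomization schedule may be kept in a locked, secured location at the clinical site".

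**The 7-day reviews.** Section 5.1.1, in the text after Table 4, says of the tables sent for review: "These data may be un-blinded based on the" medical judgement of the reviewer. Section 9.1.8 repeats this discretion for the reviewers in the plural. Neither place mentions an emergency or the Medical Monitor. On who reviews, section 5.1.2 says that "a blinded safety report will be generated and reviewed by a panel consisting of the Investigator and two independent, expert medical advisors". The synopsis and sections 5.1.1 and 9.1.8 likewise list the Investigator with two advisors. Section 5.1 names external advisors only.

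**The log.** Section 6.6: "This randomization number and treatment will be recorded along with the two-digit screening number for each subject on the Study Vaccine Accountability Log". Section 6.5.5: "The Investigator or designee will sign all study vaccine accountability forms at the end of the vaccination period".

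**Who assigns causality.** Section 9.1.6: "The Investigator must make the determination of relationship to the test article for each adverse event". Section 8.1.1.1 includes relationship in the primary safety endpoints for the 2-hour, 7-day and 21-day windows after each dose.

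**The intended blind.** Section 6.2.2 gives administration to an un-blinded staff member with no other part in the study. Section 6.3.2 leaves only the dose level open to clinic staff and says that the allocation to vaccine or placebo is to be maintained.

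**The concern.** The protocol has one rule for breaking the code and a second, looser route that the rule does not mention. The person who may gain access by that route also decides whether each event is attributed to the vaccine. Two further arrangements point the same way: a log carrying treatment that the Investigator may sign during follow-up, and a single document holding every emergency code.

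What is at stake is the objectivity of the relationship assessments. Section 11.1.2.2 compares the safety endpoints of each dose level with placebo, and one stopping criterion in 9.1.8 counts serious events judged probably related. An assessor who knows which subjects had placebo may attribute events differently by arm, in either direction. Sample size and alpha are not affected.

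**Working it through.** The check is mainly one of text, with some arithmetic on timing.

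**1. The two routes side by side**

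| | 6.7 | 5.1.1 and 9.1.8 |
| --- | --- | --- |
| Trigger | Emergency in which a subject's treatment depends on the code | Reviewers' medical judgement |
| Permission | Sponsor Medical Monitor | None stated |
| Who may learn codes | Not stated | Not stated; the panel includes the Investigator (5.1.1, 5.1.2, 9.1.8) or is external only (5.1) |
| Level | Schedule in one envelope | Not stated: group, single subject or cohort |

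Section 6.7 admits no exception beyond emergencies, so the columns cannot both stand as written.

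**2. Does partially double-blind explain it?** No. Under 6.3.2 the open part is the dose level. Vaccine versus placebo is the part meant to stay blinded, and it is what a code break reveals.

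**3. When could codes become known, relative to the relationship windows?** Those windows end 21 days after dose 2, at a subject's Day 42. From section 5.1.2 and Figure 2, first doses fall on study Days 0–3 (Cohort 1), 12–15 (Cohort 2) and 24–27 (Cohort 3).

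- *First review of Cohort 1.* The last subject completes Day 7 on study Day 3 + 7 = 10, and Cohort 2 starts on study Day 12. Cohort 1 subjects are then between 10 − 3 = 7 and 12 − 0 = 12 days from first dose. Remaining to Day 42: 42 − 12 = 30 to 42 − 7 = 35 days, including the whole period after dose 2.
- *Signing of the log.* If the end of the vaccination period means the last dose in the study, that is study Day 27 + 21 = 48.
  - Cohort 1 reached Day 42 on study Days 42–45, so its windows have closed.
  - Cohort 2 reaches Day 42 on study Days 54–57: 54 − 48 = 6 to 57 − 48 = 9 days remain.
  - Cohort 3 reaches Day 42 on study Days 66–69: 66 − 48 = 18 to 69 − 48 = 21 days remain.
- *After Day 42.* Events are still collected and causality is still assigned up to Day 228, which is 228 − 21 = 207 days after a subject's second dose. The endpoint for that later period is occurrence of events, not relationship.

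**4. How far does one code reach?** Section 5.1.2 doses each cohort in daily sets of 1 + 1, 3 + 1, 4 + 1 and 4 + 1 (vaccine + placebo). Learning that one subject had placebo therefore gives away all 2, 4, 5 or 5 codes in that day's set. The envelope holds the schedule itself, so opening it puts every code on it in view of whoever opens it.

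**The case against.** **The text does not expressly give the Investigator codes.** The un-blinding sentence in 5.1.1 closes a paragraph about material for the safety experts, and 5.1 names only external advisors, so the reviewer could mean the advisors alone. That is a possible reading. But the panel in 5.1.2 and 9.1.8 includes the Investigator, and nothing limits the discretion to the other two members. The ambiguity is itself part of what needs settling.

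**A review-stage un-blinding need not expose a cohort.** A reader might infer that any such step reveals all 16 subjects. The documents do not support this: the sample tables in Appendix C are mostly counts and percentages, and un-blinding could be by group or for one subject.

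**The log route is only a possibility.** Section 6.5.5 allows a designee to sign, and other provisions show an intent to protect the blind (6.2.2; 12.4.2 withholds assignments from auditors). This stands. What is missing is any rule on who keeps the log and who may read it. A reader might also infer that signing it opens all 48 subjects' endpoints to bias. Step 3 shows otherwise: Cohort 1's relationship windows have closed by then, and Cohort 2's nearly so.

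**Solicited intensity is graded by the subjects.** Correct (5.1.5.3, Appendix A). The point is confined to relationship.

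**The single envelope contradicts nothing.** Correct; storing it is also optional, and it must be sealed and locked. It is a weakness in the safeguard, not an inconsistency.

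**The Investigator needs information to judge escalation.** This is the real cost of a stricter rule and is taken up in the fix.

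Two further inferences fail. The Day 42 interim report is not shown to be a code break: no section says that it gives subject-level codes to the site or to the laboratory measuring antibody titres. And significance thresholds at 12 per arm would apply to any misclassification at that sample size, so they do not measure this defect.

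**Conclusion.** The point holds in this form. Section 6.7 and the un-blinding discretion in 5.1.1 and 9.1.8 contradict each other, and the log and envelope arrangements add unguarded routes to the same information. The Investigator can therefore learn vaccine or placebo codes while relationship is still being judged, against the protocol's own intent.

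The size is a window of opportunity, not an estimated bias: up to 30 to 35 days of a Cohort 1 subject's 42-day period after the first review, and 6 to 9 days (Cohort 2) or 18 to 21 days (Cohort 3) after the log is signed. These figures assume the planned calendar in Figure 2, a study-wide reading of the end of vaccination, un-blinding that actually takes place at subject level, and the Investigator rather than a designee signing. The documents permit each of the last two and require neither. The matter should be corrected, but it does not undermine the design.

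**What to change.** 1. **Reconcile 5.1, 5.1.1, 5.1.2, 6.7 and 9.1.8.** Name review-stage un-blinding in 6.7 as an exception, with a written record of who un-blinded what, when and why. Subject-level codes go to the two independent advisors. The Investigator's causality assessments for the events under review are recorded beforehand. Make the panel's membership the same in every section.
2. **Log custody (6.5.5, 6.6).** The un-blinded staff member of 6.2.2 keeps and signs the log that carries treatment. Blinded assessors have no access until database lock.
3. **Emergency codes (6.7).** Hold one sealed code per subject in place of one schedule. Where the opened code is placebo, the composition of the daily sets still gives away that day's other codes, so this limits exposure without removing it.

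The cost is wording and 48 individual codes; the un-blinded role already exists. The one downside is that the Investigator takes part in the reviews without subject-level codes unless an emergency break under 6.7 applies. Dose, schedule, sample size and alpha are unchanged.
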